## 3.9 Data analysis

We will use STATA version 15 software for statistical analyses. The differences between the control and intervention groups on baseline demographics, biological and behavioral measures will be assessed using nonparametric (chi square test) and parametric tests(t-test) as appropriate. Generalized estimating equations (GEE) approach of Zegar and Liang(Zeger & Liang, 1986) will be used to analyze how BP vary over the six months after adjusting for intervention group, baseline characteristics and healthy diet while adjusting for demographic characteristics. For the secondary outcome variables, we will use GEE analysis for changes in BMI and mixed model analysis of changes in WHtR after adjusting for the interventions ,baseline characteritics and use of antihypertensives. The GEE model will be used to examine the association between the CHW intervention with BP control and normal BMI, reporting odds ratios, after controlling for baseline measurements and use of antihypertensive medication. Statistical significance will be considered at P < 0.05.

##

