An adapted WHO stepwise questionnaire will be used to collect information on demographic characteristics, history of hypertension, other cardiovascular disease (CVD) risk factors, and health behaviours participants at baseline and follow-up visits. The international physical activity questionnaire (IPAQ) will be used to collect data on physical activity. To assess the outcome of the intervention survey will be conducted at baseline, 3 months and 6 months. The research assistants will be blinded to the randomization status of the participants. We will use STATA version 15 software for statistical analyses. The differences between the control and intervention groups on baseline demographics, biological and behavioral measures will be assessed using nonparametric (Wilcoxon rank-sum test, chi square test) and parametric tests(t-test) as appropriate. Generalized estimating equations (GEE) approach will be used to analyze how BP vary over the six months after adjusting for intervention group. This study will not only provide an innovative approach to the management of hypertension through CHW primary health prevention but will also provide preliminary data on feasibility and acceptability of integrating CHW in the control of hypertension for a future fully- powered RCT.

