## 3.4 Sample size and power calculation

With changes in BP as the primary outcome we calculated a sample of 52 between the 2 groups to show changes in BP between the intervention and control groups at a significance level of 0.05 for a two-sided test with 80% statistical power of finding a large effect (*Cohen’s d*=0.80). This study will be underpowered to find significantly small effect (*Cohen’s d*=0.30) and moderate effect (*Cohen’s d*=0.50), however, we will be able to calculate an effect size and the direction of its impact.

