## 3.6 Data collection

An adapted WHO stepwise questionnaire will be used to collect information on demographic characteristics (age, sex, occupation), history of hypertension, other CVD risk factors, and health behaviours (smoking, alcohol drinking, diet, and physical activity) of participants at baseline and follow-up visits. The international physical activity questionnaire (IPAQ)(Craig et al., 2003) will be used to collect data on physical activity. The tools will be translated and validated in the local context. We will collect detailed data on patients care cascade during the home visits and monitor their ability to control their BP with the combination of medical management and the CHW intervention. Three BP measurements, body weight, height and waist circumference will be obtained at each data collection visit by outcome assessors masked to intervention assignment.

The primary outcomes will be the differences in systolic and diastolic BP changes from baseline to the end line survey. Secondary outcomes will include the proportion of patients with controlled hypertension (BP <140/90 mm Hg) ) according to the Kenyan national guidelines(Division of Non-Communicable Diseases-Ministry of Health, 2018), body composition – Body mass index(BMI), waist circumference . Low physical activity will be defined as less than 150 minutes of moderate physical activity or 75 minutes of vigorous activity each week. To assess the outcome of the intervention the survey conducted at baseline will be conducted at 3 months of follow-up and at the end of 6 months of intervention.

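### The primary GEE in section 3.9 names no parameter that estimates the declared primary outcome, the between-arm difference in BP change to month 6

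*Protocol*

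**What the plan says.** Section 3.6 defines the target: "The primary outcomes will be the differences in systolic and diastolic BP changes from baseline to the end line survey". The same section sets the assessments: "the survey conducted at baseline will be conducted at 3 months of follow-up and at the end of 6 months of intervention". End line is therefore month 6, with one intermediate reading at month 3.

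Section 3.4 takes BP change as the outcome for sizing. It says "we calculated a sample of 52 between the 2 groups", "at a significance level of 0.05 for a two-sided test", with 80% power for Cohen's d = 0.80.

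Section 3.9 gives the only analysis of BP as a continuous outcome, a GEE that "will be used to analyze how BP vary over the six months after adjusting for intervention group", with baseline characteristics, diet and demographic characteristics as further adjusters. The Abstract has the same formulation: "Generalized estimating equations (GEE) approach will be used to analyze how BP vary over the six months after adjusting for intervention group".

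For the binary secondary outcomes, section 3.9 is worded differently and makes the intervention the exposure of interest: "The GEE model will be used to examine the association between the CHW intervention with BP control and normal BMI". Those models also control for baseline measurements. For BMI, the section speaks of modelling changes.

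**The concern.** The primary outcome is a contrast between arms at one time point: the difference in change from baseline to month 6. The sentence that should deliver it instead takes the time course of BP as its subject and lists the intervention among the things to adjust for. It does not mention change, a month-6 contrast or an arm-by-visit term, and it does not say whether the baseline reading is an outcome, a covariate or both.

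Several models fit that sentence, and their group coefficients estimate different quantities. The choice among them could be made after the data are seen. It matters more than usual here. Section 3.4 concedes low power for small and moderate effects and relies on being able to report an effect size and its direction, and the Abstract and section 1.2 offer the results as preliminary data for a fully powered trial. An effect size averaged over visits and read as the month-6 effect would mislead that planning.

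**Working it through.** **Inputs from the protocol.** Total n = 52, two-sided alpha 0.05, power 80%, d = 0.80 on BP change (section 3.4); readings at baseline, 3 and 6 months (section 3.6).

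**Assumptions, not in the protocol.** Allocation 1:1 (26 per arm), no loss to follow-up, compound symmetry, and between-visit correlation r varied over 0.3, 0.5 and 0.7. The SD of change is set to 1, so the variance of a single reading is s² = 1/[2(1 − r)].

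**Step 1: reproduce the plan's figure.** A two-sample t-test with d = 0.80 needs 25.52 per arm, so 26 per arm and 52 in total, as stated. Power at 26 per arm is 80.7% by the t-test and 82.2% by the normal approximation. The sizing is thus that of a comparison of change scores.

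**Step 2: what the group coefficient estimates.** Let the between-arm differences be 0 at baseline (by randomisation), e at month 3 and 0.80 at month 6.

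- Reading A: all three visits are outcomes and group is a covariate only. The coefficient is (0 + e + 0.80)/3. With e = 0.80 it is 0.53, or 2/3 of the month-6 effect. With e = 0.40 it is 0.40, or 1/2.
- Reading B: months 3 and 6 are outcomes, baseline BP is a covariate, and group is a main effect. The coefficient is (e + 0.80)/2. With e = 0.80 it is 0.80, or 100%. With e = 0.40 it is 0.60, or 75%.
- Reading C: arm-by-visit contrast of month 6 against baseline. It estimates 0.80 whatever e is.

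**Step 3: power.** For each model SE = √(2v/26), and power = Φ(effect/SE − 1.96), where v is the per-participant variance:

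- A: v = s²(1 + 2r)/3
- B: v = s²[(1 + r)/2 − r²]
- C: v = 1
- Month-6 difference adjusted for baseline BP: v = s²(1 − r²)

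Example, A at r = 0.5: s² = 1, v = 2/3, SE = √(2 × 0.667/26) = 0.226. With e = 0.80, 0.533/0.226 = 2.36 and power is 65%. With e = 0.40, 0.40/0.226 = 1.77 and power is 42%.

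| r | A, complete by month 3 | A, half by month 3 | B, complete | B, half | C | Month 6 adjusted for baseline |
|---|---|---|---|---|---|---|
| 0.3 | 88% | 65% | 99.5% | 93% | 82% | 94.7% |
| 0.5 | 65% | 42% | 98% | 86% | 82% | 91.5% |
| 0.7 | 38% | 24% | 96% | 80% | 82% | 87.9% |

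**Step 4: check of the point estimates.** One simulated GEE data set per scenario (4,000 participants, exchangeable correlation, r = 0.5, true month-6 effect 0.80) gave, for complete and half effect at month 3 respectively: A 0.52 and 0.39; B 0.81 and 0.62; C 0.85 and 0.83. Adding baseline BP as a covariate while keeping the baseline reading as an outcome gave 0.54 and 0.41, so that step alone does not remove the attenuation.

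**The case against.** The strongest reply is that section 3.9 is loosely worded and not wrong. It lists no model terms, does not say which visits are outcomes and does not exclude an interaction. Such details are often left to a statistical analysis plan, which may exist but was not available here. The baseline characteristics it lists stand apart from demographic characteristics, and the section's opening sentence on baseline comparisons covers biological measures, so baseline BP may well be among them. The study is also presented as one of feasibility and preliminary efficacy.

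Much of this stands, and it limits what can be claimed. A reader might infer that the protocol commits to a main effect averaged over all visits, that the reported effect must be too small, and that power must fall short of 80%. The text supports none of these as certain:

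- The averaged main effect is one literal reading of the sentence.
- Under reading B with a constant effect there is no attenuation, and in every case computed for B power is about 80% or higher.
- Even under reading A, power is 88% at r = 0.3 with the effect complete by month 3, because averaging also lowers the variance.
- The power figures depend on a correlation that the protocol does not give.

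The reply does not remove the mismatch. The protocol does specify an analysis for its primary outcome, and that specification treats the intervention as an adjuster, in two places, while the binary secondary outcomes in the same section make it the exposure. An analysis plan could settle the model, but the protocol sentence would still not match section 3.6.

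**Conclusion.** The point holds as a mismatch between the declared primary outcome and the stated primary analysis. It is independent of how the GEE sentence is read, since none of the readings is tied to the month-6 difference in change.

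The numerical consequence does depend on the reading. Across readings A to C, and for an effect half or fully present at month 3, the group estimate runs from 1/2 to all of the month-6 effect. The attenuation factors do not depend on the correlation. The power figures do, and they also assume equal arms, compound symmetry and no loss.

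It would be wrong to conclude that the sample size is in error: 52 is reproduced exactly for a change-score comparison, and it remains valid once the analysis targets that comparison or a baseline-adjusted month-6 difference.

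**What to change.** In section 3.9, and correspondingly in the Abstract, state the primary model separately for systolic and diastolic BP: readings at 3 and 6 months as outcomes, with arm, visit, arm-by-visit and the baseline value of the same measure as terms. Name the adjusted between-arm difference at month 6, with its 95% CI, as the primary estimate, and the 3-month contrast as secondary.

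An acceptable equivalent is to keep all three visits as outcomes and name the arm-by-visit contrast of month 6 against baseline. It has the same target and matches the sizing in section 3.4 (about 81% by t-test). Under the assumptions above, the baseline-adjusted form has power of 87.9% to 94.7%.

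The cost is wording only. BP is already measured at all three visits, and the sample size stays at 52.

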# METHODOLOGY

3.1 Research design

This will be a randomized controlled trial (RCT). Hypertensive patient will be randomised to either CHW led lifestyle intervention or usual care arm. The intervention will be implemented for 6 months with outcome assessment at 3 and 6 months.

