## 3.7 Data for feasibility and acceptability assessment

At the end of the study, participants in the intervention arm will complete the Client Satisfaction Questionnaire(Larsen et al., 1979) to assess acceptability of the CHW intervention. In addition, 10 patients (purposively sampled to include both gender and different age groups) and CHWs from the intervention group will be targeted for in-depth interviews (IDIs) to understand their experiences and perceptions on the utility of the intervention in the control of hypertension. The IDI guide will cover questions on experiences from using the intervention and determinants of its use. We will assess feasibility of the intervention by examining recruitment rates, follow-up home visits completion rate, dropouts, and adherence to the individualized physical activity program.

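### Unweighted GEE for BP may bias the 6-month contrast if dropout after month 3 depends on 3-month BP differently by arm; a likelihood mixed model would protect against this at little cost.

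*Protocol*

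**What the plan says.** Section 3.6 defines the endpoint: "The primary outcomes will be the differences in systolic and diastolic BP changes from baseline to the end line survey". Section 3.1 sets the visits: "The intervention will be implemented for 6 months with outcome assessment at 3 and 6 months". There are thus two post-baseline BP values per patient, and the second carries the primary comparison.

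Section 3.9 names the estimator. GEE, with a citation to the method's original description, "will be used to analyze how BP vary over the six months after adjusting for intervention group", and the covariates are "intervention group, baseline characteristics and healthy diet while adjusting for demographic characteristics". For two secondary outcomes, "we will use GEE analysis for changes in BMI and mixed model analysis of changes in WHtR". The section states no working correlation, weighting or imputation, and gives no reason for treating these continuous outcomes differently.

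Dropout appears only as a feasibility measure in section 3.7: "We will assess feasibility of the intervention by examining recruitment rates, follow-up home visits completion rate, dropouts". No dropout rate is assumed, and section 3.4 states no allowance for loss in the total of 52.

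**The concern.** Standard unweighted GEE is not generally consistent when the chance of a missing visit depends on an outcome already observed. A correctly specified likelihood model is, because it uses the 3-month BP of those who leave to inform what their 6-month BP would have been.

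Dropout that differs by arm is plausible here. Under section 3.8 only the intervention arm receives home BP monitoring, feedback on BP and monthly review of targets. A patient's decision to stay could therefore respond to the 3-month BP in one arm and not in the other.

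The estimate itself is at stake. Section 3.4 accepts that the trial is underpowered for small and moderate effects and relies on an estimated effect size and its direction. Section 1.2 says the data will inform a later, adequately powered trial. Required sample size varies with 1/effect². If a true effect of -6 mmHg were read as -4.8, the next trial would be (6/4.8)² = 1.56 times as large as needed. If it were read as -7.2, the next trial would have (6/7.2)² = 0.69 of the size needed.

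**Working it through.** **The plan's own figure.** For d = 0.80, two-sided alpha 0.05 and 80% power, the two-sample t-test needs 25.52, so 26 per arm and 52 in total, with power 0.807. The stated 52 reproduces and is not in dispute.

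**Inputs.** From the protocol: outcome visits at months 3 and 6, GEE for BP, and adjustment for baseline characteristics. Assumed, because the protocol gives no figure: SD of BP, correlations between visits, true effect, and the rate and mechanism of dropout. Also assumed: dropout occurs only after month 3, log-odds of dropout change by 1 per SD of BP, and the arm effect is visit-specific.

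**Mechanism.** With an independence working correlation, the 6-month contrast is in effect a regression among those still present at month 6. Its bias is approximately

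bias = b × (shift in intervention arm − shift in control arm),

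where the shift is how far the baseline-adjusted mean 3-month BP of those who stay differs from that of the whole arm. With equal SDs, b = (r36 − r03·r06)/(1 − r03²), where r03, r06 and r36 are the correlations baseline–month 3, baseline–month 6 and month 3–month 6. If the two shifts are equal, the bias largely cancels.

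- All correlations 0.5: b = (0.5 − 0.25)/0.75 = 0.33.
- r03 = 0.5, r36 = 0.6, r06 = 0.3: b = (0.6 − 0.15)/0.75 = 0.60.

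The second pattern should therefore give 0.60/0.33 = 1.8 times the bias of the first.

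**Large-sample results, SD 15, true effect -12 mmHg (0.8 SD), baseline BP as covariate.** Entries are bias in mmHg.

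| Dropout after month 3 | GEE independence | GEE exchangeable | Likelihood, unstructured |
| --- | --- | --- | --- |
| Completely at random, or driven by baseline BP | about 0 | about 0 | about 0 |
| Driven by 3-month BP, same way in both arms | +0.1 to +0.4 | at most about 0.1 | at most about 0.1 |
| Driven by 3-month BP, opposite by arm, correlations 0.5, base rate 10 to 30% | -0.8 to -1.9 | at most about 0.1 | within 0.1 |
| Same, correlations 0.5/0.6/0.3, base rate 10 to 20% | -1.4 to -2.5 | -0.2 to -0.3 | within 0.1 |

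The formula agrees with the simulation. At the 10% base rate, -0.77 × 1.8 = -1.39 (simulated -1.41). At 20%, -1.40 × 1.8 = -2.52 (simulated -2.48).

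**Dropout related to 3-month BP in one arm only.** With SD 15 to 18, true effect -6, about 17% loss of high-BP patients in one arm and 8% random loss in the other, independence GEE gives -4.7 to -5.4 when controls leave and -6.6 to -7.4 when intervention patients leave. That is a bias of 0.6 to 1.4 mmHg. The likelihood estimate is about -5.9 to -6.2.

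**How baseline enters the model.** SD 15, r03 = 0.3, r06 = 0.25, r36 = 0.6, true effect -6, about 18% loss of high-BP controls and 7% random loss in the other arm:

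| Analysis | 6-month contrast (mmHg) |
| --- | --- |
| GEE independence, baseline as covariate | -4.8 |
| GEE exchangeable, baseline as covariate | -6.0 |
| GEE exchangeable, baseline as a repeated outcome | -5.4 |
| Likelihood, unstructured, baseline handled either way | -6.0 to -6.1 |

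The third row is off by 6.0 − 5.4 = 0.6 mmHg.

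**The case against.** Three stronger readings are tempting, and the protocol supports none of them.

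1. A reader might infer that GEE is valid only if dropout is unrelated to earlier BP. That is too strict. Dropout that depends on modelled covariates is allowed, including baseline BP if it is among the baseline characteristics in 3.9. The simulated bias in that case is about 0.
2. A reader might infer that loss after month 3 does bias the primary result. No dropout rate or mechanism is documented. Material bias needs dropout related to 3-month BP, a relation that differs by arm, and a poorly chosen working correlation. Section 3.3.2 also excludes people who plan to relocate, and 3.8 allows outcome visits at home, which should limit losses.
3. A reader might infer that the plan already uses a dropout-tolerant model for the waist-to-height ratio. Section 3.9 says only "mixed model analysis of changes in WHtR", with no covariance structure. A plain random-intercept model implies an exchangeable covariance and is not shown to be better than exchangeable GEE.

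The strongest general objection is that the two methods can nearly coincide. With only two post-baseline visits and baseline as a covariate, exchangeable and unstructured correlation are the same single parameter. Exchangeable GEE gave -5.84 to -6.09 for a true -6, a bias of at most 0.16 mmHg. The working correlation and missing-data handling may be set in an analysis plan that is not shown, so their absence is not itself a fault. Scale matters too: with 26 per arm and SD 15 to 18, the unadjusted standard error of the difference is 15 × √(2/26) = 4.2 to 18 × √(2/26) = 5.0 mmHg, larger than any bias shown here.

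All of this stands and sets the weight of the point. It does not remove it. The choice of GEE for the primary outcome is made in the protocol, and the text as written does not secure the favourable version: neither the working correlation nor the role of baseline BP is fixed.

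**Conclusion.** The point holds as a conditional risk. If dropout after month 3 depends on 3-month BP, and differently by arm, GEE as described in 3.9 may bias the 6-month contrast. The size is about 1 to 2.5 mmHg with an independence working correlation, near 0 with an exchangeable one and baseline BP as covariate, and about 0.6 mmHg in the one scenario with baseline as a repeated outcome. The direction depends on who leaves. These figures rest on assumed SDs of 15 to 18 mmHg, assumed correlations, and assumed losses of roughly 7 to 30% per arm. None of them can be computed from the protocol. The likelihood model stayed within about 0.2 mmHg of the truth in every scenario. The change is a cheap improvement and does not correct a demonstrated error in the primary result.

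**What to change.** In section 3.9, analyse systolic BP, diastolic BP and BMI with a likelihood-based linear mixed model for repeated measures. Months 3 and 6 are the outcomes; the terms are arm, visit, arm-by-visit and the baseline value of the outcome; the covariance is unstructured and estimation is by REML. Report the 6-month arm contrast, which also ties the model directly to the primary outcome in 3.6. Keep GEE as a sensitivity analysis and state its working correlation.

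The cost is wording in 3.9. The section already names this class of model for one outcome, and the same software fits it. The downside is that the model assumes approximately normal residuals, which is reasonable for BP and BMI, and data missing at random. It does not protect against dropout driven by BP values that were never observed.

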## 3.10 Ethical considerations

The study will seek ethical approval from JKUAT Institutional ethics committee. Research permit will also be sought from the National Commission of Science Technology and Innovation. Confidentiality and anonymity of patients will be guaranteed by excluding unique identifiers from the data collected from participants. Participation in the study will be on voluntary basis and informed consent will be obtained from the patients and Community health workers (who will be respondents in the IDIs) before data collection. Results of the study will be disseminated through feedback to the participating health facilities and county department of health, conference abstract and peer referred journals.

